## 1. Introduction

### 1.1. Background

Approximately 1600 patients are diagnosed with head and neck cancer (HNC) in Denmark annually, and the incidence is increasing [1]. Oropharyngeal squamous cell carcinoma (OPSCC) constitutes one of the largest subgroups of HNC and the fastest-increasing incidence [1]. This increase is primarily driven by the rising incidence of human papillomavirus-positive (HPV+) OPSCC [2,3,4,5,6,7], which now accounts for up to 70% of all OPSCC cases in Denmark [2]. Compared with HPV-negative (HPV−) OPSCC patients, patients with HPV+ OPSCC have a distinct clinical profile, and their tumors differ both molecularly and histopathologically. HPV is a group of double-stranded DNA viruses [8], and several different high-risk genotypes exist. The most prevalent genotypes in OPSCC in Denmark are HPV16, HPV33, HPV35, HPV18, and HPV45 [2]. HPV+ patients are typically younger, have fewer comorbidities, and have a better prognosis than HPV-patients [9,10]. Despite this, 10–15% of patients with HPV+ OPSCC experience recurrence despite successful treatment, and 30% die within 5 years of diagnosis [11]. In Denmark, all patients, regardless of HPV status, treatment modality, or disease stage, follow the same standardized clinical follow-up program to facilitate early detection of recurrence. However, detecting recurrence remains challenging, as it relies on either visible findings during clinical examination or symptoms reported by the patient.

A previous study from our department demonstrated that circulating tumor HPV-DNA (ctHPV-DNA) was detectable at the time of diagnosis of HPV+ OPSCC with a sensitivity of 97%, and that ctHPV-DNA levels decreased after treatment [12]. In patients whose primary treatment was successful, ctHPV-DNA levels dropped below the limit of detection, whereas ctHPV-DNA could still be detected in the blood of patients with residual disease [12]. Reappearing ctHPV-DNA was detected in patients with recurrence up to four months before recurrent disease was diagnosed clinically [12]. These findings suggest that ctHPV-DNA testing may detect recurrence earlier than conventional clinical examination, thereby enabling earlier diagnosis and potentially earlier intervention. However, these findings require validation in a prospective setting.

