### 3.4. Outcomes

The primary endpoint is to evaluate the sensitivity and specificity of ctHPV-DNA for the detection of recurrence in patients with HPV+ OPSCC, using clinically or radiologically verified recurrence as the reference standard. Time frame: A minimum of two years and up to three years after completion of primary treatment. Sensitivity will be calculated among patients who develop recurrence, whereas specificity will be calculated among patients who remain recurrence-free.

Secondary endpoints are defined as follows:Time to recurrence detected by ctHPV-DNA.Time to recurrence detected by clinical and/or radiological examination.Number of referrals to Cancer Fast-Track examinations based on a positive ctHPV-DNA test result without evidence of recurrence.Number of PET/CT scans performed because of a positive ctHPV-DNA test result without evidence of recurrence.

Quality of life (QoL), assessed using the Danish version of the Fear of Cancer Recurrence Questionnaire (short form), will be completed by patients after receiving the result of each blood sample.

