**Figure 1 diagnostics-16-02169-f001:**

Overview of the blood sampling schedule. The first blood sample is drawn at the time of diagnosis (baseline) to assess baseline cfHPV-DNA levels before treatment initiation. The second blood sample is drawn at the first follow-up visit, two months after completion of treatment. The third blood sample is drawn six months after completion of treatment, and subsequent blood samples are collected every six months for up to three years after completion of treatment.

If a blood sample is positive at any time point after completion of treatment, the patient will be referred for a clinical examination at the Department of Otolaryngology, Head and Neck Surgery and Audiology, Copenhagen University Hospital—Rigshospitalet, followed by a PET/CT scan (supplemented by MRI if a tumor is clinically visible in the head and neck region) within 1–2 weeks. If no recurrence is detected during these examinations, blood sampling will be repeated after three months. If the additional blood sample is positive for ctHPV-DNA, a second clinical examination and PET/CT scan will be performed. If recurrence is still not detected at the additional follow-up visit, the patient will return to the standard follow-up schedule (Figure 2).

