Sensitivity analyses will explore the impact of departures from the MAR assumption. For example, alternative imputation strategies may be applied, such as assuming that patients lost to follow-up either did or did not experience recurrence. These analyses will allow assessment of the robustness of estimates for sensitivity, specificity, time to recurrence, healthcare utilization, and patient-reported outcomes.

If the results from the sensitivity analyses are consistent with the primary analyses, confidence in the validity and generalizability of the findings will be strengthened. All statistical measures of uncertainty, including 95% confidence intervals and *p*-values, will be interpreted in the context of potential bias introduced by missing data.

Patient-reported quality of life (QoL), measured using the Danish version of the Fear of Cancer Recurrence Questionnaire (short form), will be evaluated as the change between follow-up visits. Each questionnaire item is rated on a five-point Likert scale (0–4) and summed into a total score. Total questionnaire scores will be reported, and within-patient changes will be assessed using the Wilcoxon signed-rank test. For repeated measurements over time, mixed-effects models using restricted maximum likelihood estimation will be employed, with patient ID as a random effect and time points as a fixed effect.

Exploratory analyses will include correlations between ctHPV-DNA levels and clinical outcomes, including recurrence, time to recurrence, and QoL scores. Spearman’s rank correlation coefficient will be used for non-parametric data. All tests will be two-sided, and a *p*-value < 0.05 will be considered statistically significant. All analyses will be conducted in R-studio.

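### Spearman's coefficient is the only method named to relate ctHPV-DNA level to the fear score, yet both are repeated in each patient; the planned mixed model could do this better if the result were added to it

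*Protocol article*

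**What the plan says.** Section 6.3 plans the following: "Exploratory analyses will include correlations between ctHPV-DNA levels and clinical outcomes, including recurrence, time to recurrence, and QoL scores". The method follows: "Spearman’s rank correlation coefficient will be used for non-parametric data". Tests are two-sided at p < 0.05. No visit, summary measure or unit of analysis is given for the pairs.

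Both variables are serial. Sampling starts at baseline and two months after treatment; the Figure 1 caption continues (its last figure is in years): "The third blood sample is drawn six months after completion of treatment, and subsequent blood samples are collected every six months for up to three". Section 3.4 says the fear questionnaire "will be completed by patients after receiving the result of each blood sample". Section 6.3 does plan a mixed model for repeated fear scores, "with patient ID as a random effect and time points as a fixed effect", but states no ctHPV-DNA term in it.

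Section 1.1 reports that ctHPV-DNA "was detectable at the time of diagnosis of HPV+ OPSCC with a sensitivity of 97" per cent, and that levels fell below the detection limit when primary treatment succeeded.

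Sections 2.1 and 10 give the purpose of the questionnaire: to learn how the test and its results affect patients, including their fear of recurrence during follow-up.

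**The concern.** The ordinary Spearman p-value assumes independent, exchangeable pairs, in practice one pair per patient. This design yields several dependent pairs per patient. The two obvious ways to apply the test each have a drawback:

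- **Pooling patient-visits** tests whether all samples from all patients and visits are interchangeable, not whether fear is related to ctHPV-DNA. That hypothesis can fail because fear and viral DNA both fall after treatment, or because habitual fear and positivity both cluster within patients.
- **Using one visit** keeps the test valid but discards most of the positive samples.

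What is at stake is the question in Sections 2.1 and 10. A pooled p-value could be reported as evidence that viral DNA drives fear when it reflects time since diagnosis. A one-visit p-value could be read as reassurance when the test had little chance of finding an effect. The planned mixed model handles the dependence but, as stated, does not include the test result.

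**Working it through.** **The plan's own figure.** No figure is given for this correlation. The sample size in Section 4.1 supplies the patient numbers and reproduces closely: 1.96² × 0.95 × 0.05 / 0.10² = 18.25 diseased; 18.25 / 0.11 = 165.9, so 166 against the stated 167.

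**Inputs from the article.** Target 200 patients, 11% with disease, sensitivity and specificity 95% (Section 4.1); 97% detectable at diagnosis (Section 1.1); post-treatment samples at months 2, 6, 12, 18, 24, 30 and 36, so five at two years and seven at three (Figure 1 caption).

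**Assumptions not in the article.** Intraclass correlation (ICC) of the fear score 0.4-0.8; baseline fear 0-0.5 SD above later visits; runs of one to four positive samples; 0.3-0.8 SD rise in fear with a positive sample. Separate simulations varied these inputs, so ranges are shown.

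**Step 1: pooled, baseline included, no true association.** With seven later visits there are 200 baseline and 1,400 post-treatment pairs. Almost all baseline levels are positive and most later ones are zero, so Spearman is close to a baseline-versus-later comparison. For a 0.3 SD drop in fear, the naive standard error is √(1/200 + 1/1400) = 0.0756 and z is about 0.3 / 0.0756 = 4.0, twice the 1.96 threshold. It is somewhat lower in practice because some later samples are positive. Simulated rejection at nominal 5%:

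| Fear drop after baseline | Rejection |
|---|---|
| none | 0.9-2.8% |
| 0.2 SD | 59-61% |
| 0.3 SD | 93-98% |
| 0.5 SD | 100% |

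Without a drop the test is conservative, so the excess comes from the time trend and not from clustering.

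**Step 2: pooled, post-treatment visits only, no true association.** Inflation needs clustering of both fear and positivity. With fear ICC 0.5 / 0.8, rejection was:

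| Positive samples | ICC 0.5 | ICC 0.8 |
|---|---|---|
| single | 4.5% | 3.7% |
| runs of 1-2 | 7.5% | 8.8% |
| runs of 1-4 | 15.8% | 22.5% |

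Other simulations gave 3-16%, 8-10% (runs of 1-3) and 8-18%. In a model with continuous clustering of levels, rejection was 6% with no clustering and 10-23% at level ICC 0.2-0.8.

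**Step 3: one visit.** Null rejection was 3.5-4.5%, so the test is valid. For power, 22 × 0.95 + 178 × 0.05 = 20.9 + 8.9 = 29.8 patients are ever positive, if the 5% false-positive rate is taken per patient. Suppose each is positive at k of seven visits. The number positive at any one visit is then 29.8k/7, and power at 0.5 SD is about Φ(0.5/SE − 1.96), where SE = √(1/n₁ + 1/n₀):

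- k = 1: 4 v 196, SE 0.505, power about 17%
- k = 2: 8 v 192, SE 0.361, power about 28%
- k = 3: 13 v 187, SE 0.287, power about 41%

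These are normal approximations. The Spearman simulations gave 15-38% at 0.5 SD. In one matched set, power at 0.3 / 0.5 / 0.8 SD was 16% / 30% / 62%.

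**Step 4: within-patient alternative.** In that matched set (post-treatment visits, fear ICC 0.6), a patient- and visit-adjusted analysis with patient-clustered standard errors had 81% / 99% / 100% power. Its null rejection was 6.6-8.2% across settings, so these powers are slightly flattered. With baseline pairs and a 0.3 SD drop its null rejection was 6.9%, against 95% for pooled Spearman.

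**The case against.** The article never says that visits are pooled. It is a condensed account, and an analysis plan could name the pairs. That stands: a reader might infer that the planned test will reject falsely, but the text supports only a conditional statement. The phrase in Section 6.3 about using all available data introduces the handling of missing data and does not settle the matter.

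The largest inflation needs two things that the article does not establish: baseline fear pairs and a fall in fear. Section 6.3 evaluates fear as change between follow-up visits, which points away from baseline; Section 3.4 refers to every blood sample, which leaves it open. The 0.3 SD drop is assumed. This also stands.

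Long runs of positive samples have little support. Most samples are six months apart, Section 1.1 reports reappearance up to four months before clinical diagnosis, and a positive sample triggers examination. With short runs, inflation from clustering is nil to modest.

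A reader might also infer that the correlation with recurrence is invalid. It is not, if one level per patient is used: simulated null rejection was 5.0%, and Spearman against a binary outcome is essentially a rank-sum test. Inflation would require recurrence status to be copied across visits, which nothing in the article suggests.

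Finally, the analysis is exploratory, no power was promised for it, and patient-level summaries or change scores are other options. This limits the weight of the point. It does not remove it: Spearman is the only named method linking the result to fear, and the model that already handles repeated scores lists only time.

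**Conclusion.** The point holds as a minor improvement to an exploratory analysis. Ordinary Spearman is a poor fit to the serial level-fear data. Pooled, its p-value is not valid: false rejection is about 93-98% if baseline pairs enter and fear falls by 0.3 SD, and roughly 3-23% over post-treatment visits only. At one visit it is valid, with roughly 15-38% power at 0.5 SD, rising to about 62% at 0.8 SD, so the loss is large only for small to moderate effects. These sizes rest on the assumed fear ICC, time trend, persistence of positivity and effect size; only direction and rough magnitude should be relied on. Sensitivity, specificity, the sample size and the correlation of one level per patient with recurrence status are not called into question.

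**What to change.** In Section 6.3, replace Spearman for the fear score by the patient random-effect model already planned, fitted over post-treatment visits, with visit and the ctHPV-DNA result (or level) as fixed effects. Split the ctHPV-DNA term into the patient's mean and the deviation from it, so that within-patient and between-patient effects are reported separately, and use patient-clustered inference. Do not pool baseline pairs with later ones. Because clustered tests ran slightly above 5% in the simulations, a small-sample correction is worth naming. For recurrence status, it is enough to name the one level per patient that will be used.

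The cost is one or two sentences and a few lines of R, with no new data, visits or staff. The downside is that the within-patient estimate draws only on patients whose result changes, and intervals will be wider than naive pooled ones.

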## 7. Methods: Monitoring

### 7.1. Data Monitoring

A formal Data Monitoring Committee will not be established for this study. The study is a prospective, non-randomized diagnostic accuracy study involving serial blood sampling, without any therapeutic treatment or intervention expected to alter standard clinical care or pose more than minimal risk to participants. Therefore, no independent safety monitoring board is required.

An interim analysis will be conducted when all included patients have reached 1 year of follow-up. The interim analysis will include all study participants, and the results will be published in a peer-reviewed medical journal. As the study does not alter the standard treatment or follow-up program, no stopping guidelines have been defined.

### 7.2. Trial Monitoring

Oversight of study conduct and data integrity will be performed by the project leader and the study investigators. The study is conducted under institutional and sponsor oversight in accordance with all applicable ethical and regulatory requirements.

## 8. Ethics

### 8.1. Research Ethics Approval

This study has been approved by the Ethics Committee of the Capital Region of Denmark (H-23071576) and the Data Protection Office at Rigshospitalet (Forskningsjura; p-2023-15163).

### 8.2. Protocol Amendments

Any protocol amendment will be submitted to the Ethics Committee of the Capital Region of Denmark and must be approved before changes to the study are implemented.

### 8.3. Consent or Assent

Oral and written informed consent are obtained from all patients before inclusion in the study. Each patient will receive written information about the study together with the information pamphlets issued by the National Committee on Health Research Ethics describing participants’ legal rights. Thereafter, a member of the research group provides an oral presentation of the study and obtains written informed consent.

### 8.4. Confidentiality

All collected data will be kept confidential and stored in a secure REDCap database [22,23]. Each participant will be assigned a unique study identification number.

### 8.5. Ancillary and Post-Trial Care

No specific arrangements have been made for ancillary care or post-trial care. Participants will receive relevant treatment in accordance with standard healthcare practice and national DAHANCA guidelines. In the event of harm resulting from study participation, participants are covered by the national patient compensation scheme, as regulated by the Danish Act on the Right to Complain and Receive Compensation within the Health Services and administered by the Danish Patient Compensation.

## 9. Expected Results

This study uses the same ddPCR assay as our previously published retrospective study, which demonstrated a sensitivity of 97.2% for detecting ctHPV-DNA at the time of diagnosis in patients with HPV+ OPSCC and showed promising results for identifying residual disease or recurrence [12]. Based on these findings, we expect the assay to demonstrate high sensitivity and specificity for the prospective detection of recurrence.

## 10. Discussion

This study protocol outlines a prospective investigation of the sensitivity and specificity of ctHPV-DNA testing for detecting recurrence in patients with HPV+ OPSCC. The study will be population-based, with all eligible patients diagnosed with HPV+ OPSCC in Eastern Denmark invited to participate. The goal is to enable earlier and more accurate detection of recurrence in this patient population. If ctHPV-DNA can reliably identify patients with recurrent disease at an earlier stage, it may facilitate timely and earlier clinical intervention while reducing unnecessary diagnostic procedures and their associated risks and side effects. Furthermore, patients diagnosed and treated at an earlier stage typically undergo less extensive treatment, which is associated with fewer permanent side effects than treatment for patients diagnosed with advanced disease.

Additionally, patients in post-treatment follow-up programs often worry about recurrence, which can significantly impact their quality of life. Currently, detection of a recurrence relies on the presence of symptoms or visible tumor recurrence during clinical examination. Clinicians can therefore only rule out clinically evident recurrence. The presumed high sensitivity of ctHPV-DNA testing for detecting recurrence may therefore provide patients with a greater sense of reassurance during follow-up and also provide clinicians with a reliable tool for recurrence detection. The main concern with ctHPV-DNA testing is the occurrence of positive ctHPV-DNA blood samples without evidence of clinical recurrence. This uncertainty could understandably increase patients’ anxiety. However, by including the Danish *Fear of Recurrence Questionnaire*, we will be able to assess how test results influence patients’ fear of recurrence throughout the study.

The existing literature on ctHPV-DNA in HPV+ OPSCC is limited by relatively small study populations, short follow-up, or only sporadic sampling during follow-up, and frequently focuses exclusively on HPV16-positive OPSCC [24,25,26,27,28,29,30]. This protocol addresses these limitations by including a large study population followed prospectively and systematically, with ctHPV-DNA blood sampling at baseline and at every follow-up visit after treatment completion, including clinical action on positive results. In addition, this study investigates a wide panel of HPV genotypes.

## Figures and Tables

**Figure 2 diagnostics-16-02169-f002:**
[figure not shown]
Flowchart illustrating the clinical management algorithm following ctHPV-DNA blood test results.

## Data Availability

According to Danish data protection law, data from this study are not allowed to be made publicly available. Transfer of data requires permission from the Danish data protection authorities for the specific transfer. This can be applied for upon request to the corresponding author.
